##### Secondary Outcomes

Secondary outcomes include adherence and persistence on PrEP (for those who initiated PrEP). PrEP adherence will be assessed using (1) dried blood spot testing at 3-, 6-, and 9-month follow-ups, which will quantify tenofovir-diphosphate and emtricitabine-triphosphate in red blood corpuscles [45-48]. Tenofovir-diphosphate ≥700 fmol/punch will be defined as optimal adherence; and (2) self-reported adherence, which will be measured using the validated Visual Analog Scale [49]. Persistence on PrEP will be measured based on the completion of quarterly PrEP visits (recorded on the app).

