##### Procedures

After meeting eligibility, participants will provide written consent and complete a baseline assessment. Participants will then be randomized (1:1) to either JomPrEP or TAU. Participants in both groups will have JomPrEP installed on their phones and be guided through its use. However, participants in the TAU group will receive JomPrEP with major intervention features inactivated. They will have access to only the resources center with information on HIV testing and PrEP, mental health, and addiction support services, and the chat function to contact the research staff. The research staff will assist in downloading the app and provide a tutorial on how to use the app.

Participants in the JomPrEP group will be provided with full app access, including a customizable page (*visual representation using avatars and pseudonyms*); visual dashboard (*tracking PrEP adherence, daily mood tracker*); HIV testing plan (*ordering self-testing kits, testing site locator*); PrEP Care Plan (*PrEPxpress—HIV risk assessment, scheduling and managing appointments, e-consult, an electronic script for PrEP medicine, discrete door-to-door delivery, accessing test results*); mental health support (*screening for psychiatric and substance use disorder, referral to mental health support services*), chat function (*ability to chat with clinical and research staff*); tailored notifications (*automated reminders for follow-up care*); and resources center (*multimedia library on information and resources on HIV testing, PrEP, risks, relationships, and psychiatric and substance use disorder*). The research staff will use an onboarding checklist to orient participants to download JomPrEP and its use. Participants will be encouraged to explore and use all components of JomPrEP. Participants can earn points for completing specific tasks on JomPrEP (ie, gamification) and personalize the frequency, timing, and content for reminder notifications and follow-up PrEP services. They can also contact the research or clinical staff using the chat function for support. Anyone identified at baseline who seroconverts during the study period will be referred to appropriate HIV treatment services.

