	**PrEP^b^** **adherence^c^**											
		Dried blood spot testing					✓		✓		✓	
		Visual Analog Scale					✓		✓		✓	
		Online PrEP script^c,d^					✓		✓		✓	
	PrEP persistence^c^						✓		✓		✓	
Focus groups												✓
Payment						✓		✓		✓		✓

^a^Treatment as usual (restricted access to the JomPrEP app features).

^b^PrEP: pre-exposure prophylaxis.

^c^Only applies to those who initiated PrEP.

^d^Only applies to the JomPrEP group.

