##### Analytical Plan

To test the hypothesis that the intervention group (I=JomPrEP) will be significantly more effective than the TAU group for HIV testing and PrEP uptake, we will compare the proportion for both outcomes. The null hypothesis is that the proportion of HIV testing and PrEP uptake in the intervention group and TAU is equal, expressed as follows: H_0_: p_I_=p_TAU_, where p_I_ and p_TAU_ are the proportion of HIV testing and PrEP uptake in the JomPrEP and TAU groups, respectively. Our alternative hypothesis is H_1_: p_I_>p_TAU._ We will use both intent-to-treat (ITT) and on-treatment analyses, with ITT used for efficacy. Baseline characteristics will be tested for homogeneity across the 2 groups using a *t* test or Wilcoxon rank sum test for continuous variables and chi-square test or Fisher exact test for categorical variables. Any baseline variable showing a significant difference at *P*<.05 between the 2 groups will be put into the model for adjustment. For all outcome variables assessed over a 9-month follow-up period, plots of longitudinal data over time will be provided. Prior to the primary analysis, the distribution of the missing data pattern will be examined across the 2 groups. For a subgroup of those starting PrEP, we will compare PrEP adherence using the same method and PrEP persistence using time-to-discontinuation and Cox proportional hazards ratios.

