The framework for testing the study hypotheses will compare the differences between the 2 groups (JomPrEP vs TAU) over time. To test our primary hypotheses on binary outcomes of HIV testing and PrEP uptake, a generalized linear mixed model [50] with random subject effects will be built to account for the correlation in repeated measurements within participants. Treatment assignment, time, the interaction between time and treatment assignment, and any other hypothesized confounders will be included as covariates. HIV testing and PrEP uptake proportion at the 9-month follow-up will be estimated and compared using a linear contrast statement in SAS PROC GLIMMIX. Similar analyses will be conducted for the secondary binary outcomes: optimal adherence and PrEP persistence. As an alternative analytical plan for assessing the impact of the 2 groups on adherence to PrEP, continuous adherence variables will be analyzed using a linear mixed model [50] with the same set of covariates as the binary adherence outcome and percent changes in adherence between the different assessment points will be estimated and compared between the 2 arms using the linear contrast statement in SAS PROC MIXED. For the aforementioned model, the covariance structure will be selected based on the fit statistics (eg, Akaike information criterion and the Bayesian information criterion) [51]. Given the several strategies by which PrEP adherence will be measured, we will utilize Spearman correlation coefficients and scatterplots to assess the associations between the biomedical measure (dried blood spot) [45-48] and self-report measure (Visual Analog Scale) [49].

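### PrEP persistence is read from visits recorded on the app, but the TAU version of the app has no visit functions and no other source of TAU visits is named

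*Protocol article*

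**What the plan says.** **Definition.** Phase IIA, Secondary Outcomes: "Persistence on PrEP will be measured based on the completion of quarterly PrEP visits (recorded on the app". No second source is given for this outcome.

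**TAU app.** Procedures: "participants in the TAU group will receive JomPrEP with major intervention features inactivated". It continues: "They will have access to only the resources center with information on HIV testing and PrEP" (the sentence goes on to mental health and addiction support information), plus a chat with research staff.

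**JomPrEP app.** The same section lists, for the JomPrEP arm only, a PrEP care plan with "scheduling and managing appointments, e-consult, an electronic script for PrEP medicine, discrete door-to-door delivery, accessing test results".

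**Who is compared.** Study Design names persistence as a secondary outcome of JomPrEP versus TAU. Table 1 schedules it at 3, 6 and 9 months for all PrEP initiators. The footnote "Only applies to the JomPrEP group" sits on the online PrEP script and not on persistence.

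**Analysis.** The Analytical Plan says that those starting PrEP will be compared on "PrEP persistence using time-to-discontinuation and Cox proportional hazards ratios". Later it says: "Similar analyses will be conducted for the secondary binary outcomes: optimal adherence and PrEP persistence". These are the mixed-model analyses with a 9-month contrast.

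**The concern.** An outcome compared between randomized arms has to be captured in the same way in both. Here the only named recording channel is the intervention itself. The functions that would naturally leave a visit record are switched off for control participants.

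A TAU participant who starts PrEP and attends every quarterly visit with some other provider may therefore leave no trace in the named source, while a JomPrEP participant with the same behavior is counted as persistent. An apparent benefit on persistence could then reflect how visits were logged and not whether participants stayed on PrEP. Randomization gives no protection, because the distortion arises after allocation.

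**Working it through.** **1. Side by side.**

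| Item | JomPrEP | TAU |
|---|---|---|
| Appointments, e-consult, script, test results in the app (Procedures) | Yes | Not listed |
| Persistence assessed (Table 1) | Initiators | Initiators |
| Source of visit data (Secondary Outcomes) | App | App, the only source named |
| Self-report plus medical record review (Primary Outcomes) | HIV testing and PrEP uptake | HIV testing and PrEP uptake |
| Clinic dashboard (Results) | Affiliated clinics, for care of app users | Not said to cover TAU care |

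The authors restricted one app-dependent measure, the online script, to the JomPrEP arm. They left persistence open to both arms, so a between-arm comparison is intended.

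**2. How many participants depend on this.** Inputs from Sample Size: 121 evaluable per group, 268 randomized 1:1 (134 per arm), and PrEP uptake of 50% in TAU and 60% in JomPrEP.

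- TAU initiators: 0.50 × 121 = 60.5 evaluable, or 0.50 × 134 = 67 of those randomized.
- JomPrEP initiators: 0.60 × 121 = 72.6, or 0.60 × 134 = 80.4.

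**3. The plan's own figure for persistence.** Sample Size gives 85% power at a standardized effect of 0.5. For a comparison of means, power = Φ(0.5 × √(n₁n₂/(n₁+n₂)) − 1.96), two-sided 0.05. With 80.4 and 67: 0.5 × √(80.4 × 67/147.4) = 3.02, so Φ(1.06) = 85.6%. The stated figure is reproduced, and it takes for granted usable data on every initiator in both arms.

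**4. If unrecorded TAU visits count as missing.** Suppose half of the TAU initiators have no usable record, leaving n₂ = 33.5 (an assumption). Then 0.5 × √(80.4 × 33.5/113.9) = 2.43, and Φ(0.47) = 68%. With no TAU records there is no comparison.

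**5. If unrecorded TAU visits count as non-persistence.** Assumptions not in the documents: equal true persistence p in both arms, full capture in JomPrEP, a captured fraction s in TAU, 80 versus 67 initiators, and a one-sided 0.05 test of two proportions.

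- Apparent difference: d = p − ps.
- P(false positive) = Φ((d − 1.645 × SE₀)/SE₁), where SE₀ is the pooled and SE₁ the unpooled standard error.
- Example, p = 0.70 and s = 0.90: d = 0.07; pooled proportion (80 × 0.70 + 67 × 0.63)/147 = 0.668; SE₀ = 0.0780; SE₁ = 0.0781; Φ(−0.746) = 0.228.

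| TAU capture (p = 70%) | Spurious difference | P(false positive), nominal 5% |
|---|---|---|
| 95% | 3.5 points | 12% |
| 90% | 7 points | 23% |
| 80% | 14 points | 55% |
| 70% | 21 points | 83% |
| 50% | 35 points | over 99% |

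At 90% capture the false-positive rate is 15% if true persistence is 50%, and 31% if it is 80%. With the evaluable counts (73 versus 60) and p = 70%, capture of 90%, 80% and 70% gives 21%, 51% and 80%. A modest shortfall in TAU recording is enough to matter.

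**The case against.** **TAU visits might still be recorded.** Procedures lists what TAU participants can use, not who records visits. Both arms have the app installed, and Results describes a dashboard for affiliated-clinic staff that works much like a health record. Staff could in principle log a TAU visit there. A reader might infer that TAU visits cannot appear at all and that measured TAU persistence would be near zero. The documents do not support that as fact: it is the worst case, and it also needs a rule scoring absent records as failure, which is not stated. The dashboard does not close the gap, however. It is described for the care of app users at affiliated clinics, and nothing says that it captures TAU care or care elsewhere.

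**The bias need not favour JomPrEP.** This is correct. If absent records are treated as missing, the result is lost control data and not necessarily a tilt toward JomPrEP.

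**Two analyses can coexist.** A reader might call the Cox and mixed-model analyses contradictory, with the choice left until results are seen. They answer different questions, and an analysis plan that is not shown may rank them. What can be said is that the article does not rank them: its one explicit alternative, "As an alternative analytical plan for assessing the impact of the 2 groups on adherence to PrEP", concerns adherence only.

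**Event times.** A reader might also infer that a Cox model would have only three possible event times. This is not established. Participants enter off PrEP and may start on different dates, and Table 1 shows when persistence is assessed, not how discontinuation is dated.

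**Conclusion.** The concern holds as an ascertainment problem. The article names a source for persistence that its own description of the TAU app does not support, uses that source for a between-arm comparison, and names no other. This goes beyond detail that an article leaves to a fuller document, because the stated rule itself conflicts with the stated control condition.

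About 60 evaluable TAU initiators are affected under the planned uptake. The direction and size of the distortion depend on two things not stated: how completely TAU visits reach the app or dashboard, and how absent records are scored. The false-positive rates rest on assumed capture and persistence and show sensitivity; they are not predictions.

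The outcome is secondary, and the comparison of HIV testing and PrEP uptake does not rest on this definition. The change should be made, but the point does not undermine the trial's main question. The absence of a named main persistence analysis is minor.

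**What to change.** 1. **Same source in both arms.** Ascertain persistence from self-reported PrEP use and PrEP visits at 3, 6 and 9 months, confirmed by the medical record review already planned for the primary outcomes.
2. **Count from initiation.** Judge persistence as continued use or visits since each participant's own PrEP start. Current use at month 9 alone would largely repeat the primary uptake outcome and would count a very recent starter as persistent.
3. **Reassign the app record.** Keep app-recorded visits as a process measure in the JomPrEP arm only.
4. **State the scoring rule.** Say how an initiator without a confirmed visit record is classified, identically in both arms.
5. **Minor.** Name either the Cox or the binary mixed-model analysis of persistence as the main one and the other as supportive.

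**Cost.** Revised outcome wording, questionnaire items on PrEP visits if not already included, and an extension of the record review to PrEP visit dates, since it is now stated only for HIV testing and PrEP uptake. Self-report is less objective than a visit log, and confirmation from records only partly offsets this. The sample size and visit schedule do not change.

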##### Other Outcomes

Consistent with the SCT framework, we will collect measures related to its constructs, which are (1) self-regulation (frequency of use of app components, perceived HIV risk), (2) self-efficacy (related to PrEP use and adherence, condom use, substance use, and utilization of mental health support), and (3) goal setting and environmental influences (frequency of use of HIV testing, PrEP care plans, and notification reminders). Given the importance of moderating factors that may influence the uptake of prevention strategies, we will use the Socioecological Theoretical model, which links individual (eg, sociodemographic, sexually transmitted infection incidence, sexual/drug use behavior, mental health), social (eg, social support, peer norms), and structural (eg, stigma, discrimination, incarceration) factors as they relate to linkage to HIV prevention services in Malaysian MSM (Table 1).

**Table 1 table1:** Study activity and measures (phase II).

Study activity				Timeline								
				Prebaseline		Baseline		3 Months		6 Months		9 Months
**Enrollment**												
	Eligibility screen		✓									
	Informed consent				✓							
	Randomization				✓							
**Interventions**												
	App onboarding				✓							
	**Access to the app**											
		JomPrEP group			✓		✓		✓		✓	
		TAU^a^ group			✓		✓		✓		✓	
**Assessments**												
	Questionnaires				✓		✓		✓		✓	
	**PrEP^b^** **adherence^c^**											
		Dried blood spot testing					✓		✓		✓	
		Visual Analog Scale					✓		✓		✓	
		Online PrEP script^c,d^					✓		✓		✓	
	PrEP persistence^c^						✓		✓		✓	
Focus groups												✓
Payment						✓		✓		✓		✓

^a^Treatment as usual (restricted access to the JomPrEP app features).

^b^PrEP: pre-exposure prophylaxis.

^c^Only applies to those who initiated PrEP.

^d^Only applies to the JomPrEP group.

##### Analytical Plan

To test the hypothesis that the intervention group (I=JomPrEP) will be significantly more effective than the TAU group for HIV testing and PrEP uptake, we will compare the proportion for both outcomes. The null hypothesis is that the proportion of HIV testing and PrEP uptake in the intervention group and TAU is equal, expressed as follows: H_0_: p_I_=p_TAU_, where p_I_ and p_TAU_ are the proportion of HIV testing and PrEP uptake in the JomPrEP and TAU groups, respectively. Our alternative hypothesis is H_1_: p_I_>p_TAU._ We will use both intent-to-treat (ITT) and on-treatment analyses, with ITT used for efficacy. Baseline characteristics will be tested for homogeneity across the 2 groups using a *t* test or Wilcoxon rank sum test for continuous variables and chi-square test or Fisher exact test for categorical variables. Any baseline variable showing a significant difference at *P*<.05 between the 2 groups will be put into the model for adjustment. For all outcome variables assessed over a 9-month follow-up period, plots of longitudinal data over time will be provided. Prior to the primary analysis, the distribution of the missing data pattern will be examined across the 2 groups. For a subgroup of those starting PrEP, we will compare PrEP adherence using the same method and PrEP persistence using time-to-discontinuation and Cox proportional hazards ratios.

The framework for testing the study hypotheses will compare the differences between the 2 groups (JomPrEP vs TAU) over time. To test our primary hypotheses on binary outcomes of HIV testing and PrEP uptake, a generalized linear mixed model [50] with random subject effects will be built to account for the correlation in repeated measurements within participants. Treatment assignment, time, the interaction between time and treatment assignment, and any other hypothesized confounders will be included as covariates. HIV testing and PrEP uptake proportion at the 9-month follow-up will be estimated and compared using a linear contrast statement in SAS PROC GLIMMIX. Similar analyses will be conducted for the secondary binary outcomes: optimal adherence and PrEP persistence. As an alternative analytical plan for assessing the impact of the 2 groups on adherence to PrEP, continuous adherence variables will be analyzed using a linear mixed model [50] with the same set of covariates as the binary adherence outcome and percent changes in adherence between the different assessment points will be estimated and compared between the 2 arms using the linear contrast statement in SAS PROC MIXED. For the aforementioned model, the covariance structure will be selected based on the fit statistics (eg, Akaike information criterion and the Bayesian information criterion) [51]. Given the several strategies by which PrEP adherence will be measured, we will utilize Spearman correlation coefficients and scatterplots to assess the associations between the biomedical measure (dried blood spot) [45-48] and self-report measure (Visual Analog Scale) [49].

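### Baseline P<.05 tests between randomized arms help choose the covariates of the primary model, so adjustment follows chance imbalance rather than prognosis and gains almost no power

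*Protocol article*

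**What the plan says.** The Analytical Plan first compares the arms at baseline: "Baseline characteristics will be tested for homogeneity across the 2 groups using a *t* test or Wilcoxon rank sum test for continuous variables", with chi-square or Fisher exact tests for categorical variables. The result then decides the model: a variable that differs at P<.05 "between the 2 groups will be put into the model for adjustment".

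The next paragraph sets out the model for both primary endpoints: "a generalized linear mixed model [50] with random subject effects will be built to account for the correlation in repeated measurements within participants". Its terms are treatment, time and their interaction, and "any other hypothesized confounders will be included as covariates". No confounder is named. The result comes from a month-9 contrast: "HIV testing and PrEP uptake proportion at the 9-month follow-up will be estimated and compared using a linear contrast statement in SAS PROC GLIMMIX". The null hypothesis is that the two arms' proportions are equal.

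Study Design gives 1:1 randomization of 268 participants. Other Outcomes lists a broad field of individual, social and structural factors, without a count.

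**The concern.** In a randomized trial a baseline difference between arms arises by chance. A significance test on it says nothing about whether the variable predicts HIV testing or PrEP uptake, and prediction is what makes adjustment worthwhile. The screen leaves out a strong predictor that happens to be balanced and admits an irrelevant one that is not.

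Two things are at stake. The first is precision: the trial collects likely predictors at baseline, and this rule seldom uses them. The second is prespecification: part of the covariate set is unknown until the arms have been compared. If the mixed model uses a logit link (usual for binary outcomes, but not stated), the covariate set also changes the conditional odds ratio. Chance imbalance then partly influences which effect is estimated.

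**Working it through.** **1. Inputs.** From Sample Size: 50% uptake under TAU, 60% under JomPrEP, one-sided alpha .05, 121 per group, stated power 90%, and 268 enrolled (134 per group). Assumed, because the article gives no figure: the number k of candidate baseline variables, the prognostic strength of a covariate, and the between-subject SD.

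**2. The plan's own figure.** With the usual two-proportion formula,

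n = [1.645·√(2·0.55·0.45) + 1.282·√(0.25 + 0.24)]² / 0.10² = (1.157 + 0.897)² / 0.01 ≈ 423 per group.

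The stated 121 does not reproduce. Power at 121 is Φ[(0.10·√121 − 1.157)/0.70] = Φ(−0.082) = 46.7%; at 134 it is 50.0%. That is a separate and larger problem, which covariate adjustment cannot close. It matters here only because it sets the power level at which the rule operates.

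**3. How often the rule fires.** For one variable under randomization the probability is 0.05 by construction (4.5% to 5.5% in simulation). A prognostic variable therefore fails to enter by this route about 95% of the time. For at least one of k independent variables it is 1 − 0.95^k:

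| k (assumed) | 5 | 10 | 15 | 20 |
|---|---|---|---|---|
| P(at least one enters) | 23% | 40% | 54% | 64% |

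**4. What the rule does to power.** Month-9 logistic regression was simulated with one standard-normal prognostic covariate, the marginal proportions held at 50% and 60%, a one-sided .05 Wald test, and 6,000 trials per cell.

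| n per group | Assumed slope (logits per SD) | Unadjusted | P<.05 rule | Always adjusted | Gain over rule (points) |
|---|---|---|---|---|---|
| 121 | 0.5 | 49.0% | 48.9% | 49.7% | 0.8 |
| 121 | 1.0 | 48.4% | 48.5% | 53.5% | 5.0 |
| 121 | 1.5 | 49.1% | 49.3% | 58.8% | 9.4 |
| 134 | 0.5 | 50.5% | 50.5% | 52.8% | 2.3 |
| 134 | 1.0 | 50.3% | 50.5% | 57.9% | 7.4 |
| 134 | 1.5 | 49.7% | 50.3% | 61.2% | 10.9 |

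The Monte Carlo standard error of one cell is about √(0.49·0.51/6000) = 0.65 points, so the gain at slope 0.5 is small enough to be called negligible. A further simulation at 121 per group gave rule versus always adjusted of 47% vs 48%, 47% vs 52% and 47% vs 58%, the same picture.

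At 50% versus 68.5%, a difference that does give about 90% power with 121 per group, rule versus always adjusted was 91.2% vs 92.2%, 91.0% vs 94.9% and 91.8% vs 96.9%.

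**5. Type I error.** With 50% in both arms, rejection under the rule ran from 4.3% to 5.1% across the six cells. There is no inflation.

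**6. The 9-month proportions (minor).** If the link is logit with a normal subject effect of SD σ, the population proportion is p = ∫ expit(a + σu)φ(u)du. A proportion back-transformed at a random effect of zero is expit(a). For p = 50%, a = 0 and the two agree. For p = 60%, solving for a gives:

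| σ (assumed, logits) | 1 | 2 | 3 |
|---|---|---|---|
| 50% vs 60% would read | 50% vs 62% | 50% vs 66% | 50% vs 71% |

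**The case against.** **The rule is not the only way in.** A reader might infer that covariates enter solely through the P<.05 screen. The text does not support that: hypothesized confounders enter whatever their balance, so a variable expected in advance to predict uptake could be included. This stands, and it means that the loss in step 4 is what the screen alone costs, not an established loss for the trial. The defect remains, because those variables are unnamed and are described as confounders rather than as predictors of outcome.

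**Chance does not define the effect.** Imbalance decides part of the covariate set, no more. Type I error holds and power matches the unadjusted analysis. The harm is lost efficiency and weaker prespecification, not a false claim of benefit.

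**The power figures rest on assumptions.** They use one covariate, one time point and invented slopes, not the repeated-measures model. This stands, so they are given as a range.

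**Naming covariates is usually left to the SAP.** That is fair for a missing list. Here, however, the article states a selection rule, and it is the stated rule that is poor.

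**The mixed-model proportions.** A reader might conclude that the primary test does not address the stated null, or that the published proportions will be wrong. Neither follows. With a common random-effect distribution in both arms, equal conditional log-odds imply equal proportions. The article states neither the link nor the back-transformation, so step 6 shows what one coding choice would do, not what the plan prescribes.

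**Conclusion.** The point holds as a matter of efficiency and prespecification. Baseline testing at P<.05 is one stated route into the primary model. It takes no account of prognosis and yields the power of an unadjusted analysis to within about 1 point. At 50% versus 60% with 121 per group, adjusting for a prespecified covariate would add about 1 to 10 points of power over the assumed range of 0.5 to 1.5 logits per SD. The covariate set, and hence the conditional effect, also depends partly on chance imbalance.

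The size rests on the assumed slopes, a single covariate analysed at month 9, and individual randomization. The article also randomizes couples and housemates together (Minimizing Contamination Across Groups), which the simulation ignores. The documents support no claim of bias, of inflated type I error or of an invalid test of the null hypothesis. Better adjustment would not rescue the sample size. The point about proportions is a reporting safeguard only.

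**What to change.** - Delete the P<.05 rule, and present the baseline table descriptively, without significance tests.
- Replace the open hypothesized-confounders clause with a short named list of prognostic baseline variables that the trial collects. Candidates listed under Other Outcomes include sociodemographic factors, perceived HIV risk and sexual or drug use behavior.
- Fix the list before any outcome data by arm are seen, and adjust for these variables regardless of balance.
- As a minor addition, because the hypothesis is stated in proportions, report each arm's 9-month proportion and their difference as standardized estimates: average the model predictions over participants and integrate over the random effect.

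If the SAP already names a covariate list, state there that it replaces the article's rule. The cost is a change of wording and a few lines of code, with no new data or visits.
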